## **8.7. Adverse event definitions and reporting**

### **8.7.1. Adverse Event definition**

An adverse event will be defined as any untoward medical occurrence (any unfavourable and unintended sign, symptom or disease, including an abnormal laboratory finding) in temporal association with the use of the investigational treatment and may or may not be causally related to it.

Abnormal laboratory results will be reported as adverse events if the abnormality occurs or worsens after institution of the study treatment, and if they require clinical intervention or further investigation, unless they are associated with an already reported clinical event.

All safety events that require reporting to the Ethiopian authority (i.e. NHRERC and FMHACA) will be made according to the national regulations.

### **8.7.2. Serious Adverse Event**

An adverse event will be defined as serious if it is

- fatal
- life-threatening
- requires or prolongs hospitalization
- results in persistent or significant disability
- is a congenital anomaly/birth defect
- results in an important medical event that may not be immediately life threatening or does not directly result in death or hospitalization, but which may jeopardize the patient or may require intervention to prevent the other outcomes listed above.

Serious events also include any other event that is defined as serious for the specific purposes of the protocol or which is defined as serious by the regulatory agency in the country in which the event occurred.

Any prolongation of the hospitalization that is not related to a medical event but related to any social and/or financial reasons will not be considered as an SAE.

### **8.7.3. Eliciting Adverse Event information**

The investigator is required to report all directly observed adverse events and all adverse events spontaneously reported by the trial subject using concise medical terminology. In addition, each trial subject will be questioned about the occurrence of adverse events on a daily basis during the hospitalization period (day 0-29; or until day 58 in case of extended treatment), and 1 month after the stop of treatment (i.e. day 58 or day 86 in case of extended treatment) with a generic question such as “have you felt different in any way/ had any problems since starting the new treatment/the last assessment?” If the response is “Yes”, the nature of the event, the date and time (where appropriate) of onset, the duration, maximum intensity (see below) and relationship to treatment will be established (see below). Details of any

dosage/schedule modification or any corrective treatment will be recorded on the appropriate pages of the CRF.

#### **8.7.4. Adverse Event reporting period**

The adverse events reporting period for this trial begins:

- Upon administration of the first dose of study medication for non-serious and serious events and ends 1 month after the stop of the treatment when a further safety evaluation occurs.

All adverse events that occur during the adverse event reporting period specified in the protocol must be reported to DNDi, whether or not the event is considered related to study medication.

In case a patient receives the secondary prophylaxis, there will be another period of safety reporting. The reporting period starts upon administration of the first dose of Pentamidine up to a week after the last injection of Pentamidine that occurs during the study period. Only Serious Adverse Events will be collected during this period.

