4. Liposomal Amphotericin B (Ambisome®). AmBisome is considered safe even also in HIV co-infected patients. It was shown to be effective in Europe in doses of 30-40 mg/kg but it did not prevent relapses. In Ethiopia, cure rates with total dose of 30mg/kg are unacceptably low in HIV co-infected patients. MSF in Ethiopia records a 74% cure rate in primary VL. There is little information from other endemic areas; experience from a number of centres in

the state of São Paulo, Brazil seem to give similar low cure rates with monotherapy AmBisome® at 21 mg/kg total dose in co-infected patients. The official WHO recommendation is 40 mg/kg total dose based on (limited) experience in Europe (table 2).

5. Miltefosine. In a RCT in Ethiopia MF was safer than SSG but efficacy was lower with a relapse rate of 31% (also see above under SSG). It is potentially teratogenic implying the use of adequate contraceptive cover in women of child-bearing age. Because of the long-half life, this should be maintained for 4 months after treatment when used for 28 days.
6. Pentamidine. There is no information on its use in the primary treatment of VL in co-infected patients; it is mainly used as secondary prophylaxis. It is well-distributed in tissues and slowly excreted. While in previous treatment studies in HIV-negative patients toxicity is well described (mainly development of diabetes mellitus), no serious side-effects are noted when pentamidine is used as secondary prophylaxis.

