### **2.2.2 Secondary Endpoint(s)**

#### **Relapse-free survival at 12 months as defined as**

The patient being alive and disease free from day 29 (if initially cured) or day 58 (if they received an extended treatment) and remains disease free until the last follow-up assessment (i.e. day 390).

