## **7.8. Secondary prophylaxis**

Secondary prophylaxis of monthly pentamidine (4mg/kg IM) will be offered to all patients that clear parasites independently of when this is achieved (i.e. initially cured on day 29, extended treatment cured on day 58 or relapse patient that achieved cured at any point in time). Patients will be eligible for the secondary prophylaxis if their CD4 count is < 200 cells/mL and there is no contraindication (e.g. renal failure, diabetes mellitus, known hypersensitivity) for the drug used. Secondary prophylaxis will normally be continued till the patient has sufficient CD4 recovery.(i.e. over 200 cells/mL at day 390 assessment). Prophylactic treatment can be continued after the study end (day 390) if required. However, it would be stopped in case of relapse, adverse events requiring discontinuation of medication or if the patient requests to stop the prophylaxis.

The prophylaxis will be started one month after the end of the treatment and will be dispensed every month up to a maximum of 18 months.

At each of the monthly visit the glucose level will be monitored. Moreover, liver and kidney function will be performed at day 210 and 390 assessments.

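### Section 8.7.4 closes SAE reporting one week after the last monthly pentamidine injection, so whether an SAE is reportable can depend on its outcome

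*Protocol*

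**What the plan says.** Section 8.7.4 defines two safety reporting periods. The first runs from the first dose of study drug and "ends 1 month after the stop of the treatment when a further safety evaluation occurs". The second applies to patients on secondary prophylaxis: "The reporting period starts upon administration of the first dose of Pentamidine" and lasts "up to a week after the last injection of Pentamidine that occurs during the study period". In this second period, "Only Serious Adverse Events will be collected during this period". The same section ties the duty to report to the sponsor to events that fall within the reporting period.

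Section 7.8 starts pentamidine one month after the end of treatment and says it "will be dispensed every month up to a maximum of 18 months". On early ending it says "it would be stopped in case of relapse, adverse events requiring discontinuation of medication or if the patient requests to stop the prophylaxis". It also allows prophylaxis to go on after day 390.

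Three other places matter:
- Section 8.7.5 asks for every SAE to be reported within 24 hours of the investigator's awareness, without restating a period.
- Section 8.7.9 deals with following events up and does not extend the period.
- Section 10.7 plans to describe adverse events on treatment and in follow-up, with SAE narratives built from the sites' SAE reports.

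**The concern.** The end of the second period is anchored to an injection that can be identified as the last one only in retrospect. An SAE may itself decide which injection that is. If a patient dies or stops prophylaxis because of an SAE, the injection already given becomes the last, and the period has closed 7 days after it. If the patient recovers and is injected again during the study, the period stays open and the event lies inside it. Two events on the same day after injection are thus treated differently according to what followed.

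This is informative truncation among the recipients of prophylaxis. It removes fatal and prophylaxis-ending events preferentially, and those are the ones that the sponsor and the DSMB would most want documented. The first reporting period gives no cover, because it ends about when prophylaxis starts. The protocol gives no reason for allowing one week here when the study drugs get one month, and its background section says of pentamidine: "It is well-distributed in tissues and slowly excreted".

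**Working it through.** The protocol states no figure to reproduce, so the check is interval arithmetic plus a reading of the sections side by side.

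**Inputs**
- Window after the last injection: 7 days (8.7.4).
- Injection interval T: one month, taken as 28 to 31 days (7.8).
- Timing of events within the interval: not given in the protocol, so assumed and varied below.

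**Step 1: classify one event.** Take an SAE on day 15 after an injection.
- The patient is injected again during the study: the period is still open on day 15, so the SAE is inside.
- The patient dies, or prophylaxis stops because of the SAE: the period closed on day 7, so the SAE is outside.

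Any prophylaxis-ending event after day 7 follows the second line.

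**Step 2: share outside under uniform timing.** Share outside = 1 − 7/T.

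| T (days) | Covered, 7/T | Outside |
|---|---|---|
| 28 | 25.0% | 75.0% |
| 30 | 23.3% | 76.7% |
| 31 | 22.6% | 77.4% |

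**Step 3: front-loaded timing.** Let the time from injection be exponential with scale τ, truncated at 30 days. Share outside = 1 − (1 − e^(−7/τ)) / (1 − e^(−30/τ)).

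| τ (days) | Outside |
|---|---|
| 30 | 67% |
| 15 | 57% |
| 12 | 52% |
| 10 | 47% |
| 7 | 36% |
| 5 | 24% |
| 3 | 10% |

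**Step 4: a mixture.** Let a fraction f of events be acute, all within 7 days, and the rest uniform over 30 days. Share outside = (1 − f)(1 − 7/30).
- f = 0.20: 0.80 × 0.767 = 61%
- f = 0.35: 0.65 × 0.767 = 50%
- f = 0.50: 0.50 × 0.767 = 38%

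More than half of prophylaxis-ending events fall outside unless τ is below about 11-12 days or more than about a third of the events are acute.

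**Step 5: effect of a longer window.** If the window is at least T days, no event that occurs before the next scheduled injection is outside, whatever its outcome, so the share is 0%. A window to day 390 does the same within the study.

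**Step 6: does another section already close the gap?**
- 8.7.5 governs how and how fast SAEs are reported; 8.7.4 governs the period. If 8.7.5 is meant to override the period, the two sections conflict.
- 8.7.9 concerns the follow-up of events only.
- 2.2.2 makes death a failure of relapse-free survival, so deaths are known, but it calls for no SAE form.

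**The case against.** The strongest reply is that little of what the trial is built on is touched. The primary endpoint is parasitology at day 29. The safety endpoint in section 2.2.2 covers treatment plus one month, which the first reporting period serves in full. Pentamidine is prophylaxis in eligible patients, not a test regimen, the stopping rule uses no SAE from this phase, and the safety analysis is descriptive. All of this stands and limits the severity.

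A reader might infer that deaths are lost to the trial. They are not. All patients are followed to day 390 (section 8.5), section 9 asks for every effort to document outcome, and death counts against relapse-free survival. What is missing is the obligation to file an SAE form, and with it the causality assessment and the narrative.

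A reader might also state flatly that most prophylaxis-ending SAEs go unreported. The documents do not support that. The protocol gives no event timing, and the share outside drops below half if events cluster soon after injection. Reporting in practice may also be better than the text requires. When a non-fatal SAE begins, nobody knows that the previous injection was the last, and the 24-hour rule in 8.7.5 pushes the site to report at once. That leaves capture to site habit, and it does not help with a death, after which no further injection is possible.

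Nor can one say that every SAE in continuing patients is captured. The window is tied to the last injection within the study, and prophylaxis may go on beyond it. A continuing patient with an SAE more than 7 days after the last in-study injection is outside too. Finally, the rule does not simply keep the milder events: prophylaxis-ending SAEs in the first 7 days are kept, and ending prophylaxis is not a measure of severity.

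**Conclusion.** The point holds as a moderate defect in the safety reporting rules. On the text of 8.7.4 and 7.8, an SAE more than 7 days after an injection is reportable or not according to whether another in-study injection follows. That conclusion needs no assumption.

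The size does. The window covers 23-25% of an interval. The share of prophylaxis-ending events outside it is 75-77% under uniform timing and about 36-67% for front-loading with τ between 7 and 30 days; sharper clustering would lower it further. No number of events can be derived from the protocol.

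For deaths the loss is documentation and causality assessment, because the death itself enters relapse-free survival. For non-fatal prophylaxis-ending SAEs there is no second route that requires capture. The primary endpoint and the declared safety endpoint are unaffected.

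**What to change.** In section 8.7.4, replace the one-week end point in one of two ways:
- **One full injection interval** (about 30 days, and not shorter than the scheduled interval) after the last injection in the study. This removes the dependence on outcome for events before the next scheduled injection.
- **Day 390** for every patient who has had at least one injection. This also covers SAEs later in follow-up in patients who stopped early, and it gives a single end date that does not depend on what happened to the patient.

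Then state in 8.7.5 that its 24-hour rule applies to the periods in 8.7.4, and make the period agree with the plan in 10.7 to describe adverse events in follow-up.

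The change affects reporting only and leaves treatment as it is. The cost is a short amendment and a few more SAE forms. One limit should be written down: patients who have stopped prophylaxis no longer attend monthly. SAEs after the missed injection would come to light through spontaneous reports or at the scheduled day 210 and day 390 visits, so ascertainment would be less complete and later than in patients still receiving injections.

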#### **8.7.5. Adverse Event reporting requirements**

Information on adverse events must be evaluated by a physician. Each adverse event is to be classified by the investigator as serious or non-serious. This classification will determine the reporting procedure for the event.

All serious adverse events (SAE) are to be reported immediately (within 24 hours of awareness of SAE by the investigator) either by mail to the following address; [SAE\\_VL\\[contact]](mailto:[contact]) or by phone to the DNDi medical coordinator, using the SAE report form. This includes a description of the event, onset date and type, duration, severity, relationship to study drug, outcome, measures taken and all other relevant clinical and laboratory data. The initial report is to be followed by submission of additional information (follow-up SAE form) as it becomes available. Any follow-up reports should be submitted as soon as possible, and if possible within 7 working days.

Serious adverse events should also be reported on the clinical trial adverse event case report form (CRF). It should be noted that the form for reporting of SAE (SAE form) is not the same as the adverse event section of the CRF. Where the same data are collected, the two forms must be completed in a consistent manner, and the same medical terminology should be used.

Non-serious adverse events are to be reported on the CRF, which is to be submitted to DNDi as specified in the Study Documentation section of this protocol. In the CRF, a given adverse event will be recorded only one time per patient, and the severity recorded will be the maximum level reached. If several distinct episodes of the same condition occur, their number will be recorded in the CRF.

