#### **Safety**

Assessment of safety during treatment and follow-up based on clinical adverse events, laboratory parameters during treatment and 1 month (after end of initial treatment or after end of extended treatment) follow-up.

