#### **8.7.6. Grading of Adverse Event severity**

Clinical adverse events and laboratory parameters will be graded by investigator using the Common Toxicity Criteria for Adverse Events (CTC AE) version 4 (May 2009) so that comparisons can be made between treatment arms. This specific

adverse event severity grading scale is used in order to standardize reporting between investigators and sites.

In the case that an AE is not listed, the assessment of intensity/severity will be based on the investigator's clinical judgment. The maximum intensity/severity experienced should be recorded and will be assigned to one of the following categories.

- MILD - Does not interfere with patient's usual functions
- MODERATE - Interferes to some extent with patient's usual functions
- SEVERE - Interferes significantly with patient's usual functions

It is to be noted the distinction between severity and seriousness of adverse events. A severe adverse event is not necessarily a serious event.

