#### **10.7. Safety Analysis**

Adverse events will be described on treatment and during follow-up. AEs will be coded using MedDRA and tabulated by severity / CTC V4 AE grading. Causality of AEs will also be tabulated. Serious Adverse Events will be described by individual narratives based on the SAE reports provided by the site investigators. Summary statistics will be tabulated for hematological and biochemical parameters as well as for efficacy of ART (CD4 count, viral load) at each time point.

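### One CRF record per adverse event at maximum severity, with an undated episode count, cannot place recurrent non-serious events in the treatment or follow-up period

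*Protocol*

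**What the plan says.** - **Recording rule (section 8.7.5).** On the CRF, "a given adverse event will be recorded only one time per patient, and the severity recorded will be the maximum level reached". The next sentence deals with recurrences: "If several distinct episodes of the same condition occur, their number will be recorded in the CRF". Neither sentence gives an episode its own date, grade or causality. Neither says whether the single record takes its date from the first or the worst episode.
- **Elicitation (section 8.7.3).** Patients are questioned daily in hospital (to day 29, or to day 58 with extended treatment) and again one month after treatment stops. Each positive answer leads the investigator to obtain what the event was, when it began, how long it lasted, its greatest intensity and its relation to treatment.
- **Reporting window (section 8.7.4).** Collection starts with the first dose and "ends 1 month after the stop of the treatment when a further safety evaluation occurs". In the later prophylaxis period only serious events are collected.
- **Planned use.** The safety endpoint in section 2.2.2 is "Assessment of safety during treatment and follow-up based on clinical adverse events" and laboratory parameters. Section 10.7 says "Adverse events will be described on treatment and during follow-up" and "AEs will be coded using MedDRA and tabulated by severity / CTC V4 AE grading", with a causality table as well. Section 8.7.6 explains that a common grading scale is used "so that comparisons can be made between treatment arms".
- **Second course (sections 3.2 and 3.3).** Patients who are parasite-positive but clinically well at day 29 repeat the full regimen to which they were allocated.

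**The concern.** The analysis section treats time on treatment and time in follow-up as separate phases, and the design adds a repeated course for some patients. The CRF rule reduces every recurrence of an event across those phases to one line with one grade, one causality and a count.

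Take a patient who vomits mildly in the first course, severely in the second and mildly in the month after. The record holds one severe event and the number three. It does not show in which phase the severe episode fell, or whether the causality applies to an episode on or off drug. For non-serious clinical events, the AE data then cannot show reliably whether a second course brings back the same toxicity. Period-specific incidence may also be distorted, and to a different degree in each arm if early event rates differ. Safety is a stated secondary objective, and the DSMB reviews adverse events in both arms (section 10.9).

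**Working it through.** The protocol gives no figure on this point, so there is none to reproduce. The check has two parts.

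**1. What the record keeps**

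| Needed for a table by period | Elicited (8.7.3) | Kept on the CRF for a recurrence (8.7.5) |
|---|---|---|
| That an episode occurred | yes | yes, as part of a count |
| Onset date and duration | yes | not provided for |
| Grade | yes, maximum intensity | one maximum over all episodes |
| Relationship to treatment | yes | one record, so one value |

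The database is entered from the CRF (section 12.7). What the CRF does not hold cannot be restored at analysis, whatever a statistical analysis plan says.

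**2. Size of the distortion (illustrative)**

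Assumptions, none of them from the protocol: two periods; the same true per-patient probability p of the event in each; independence between periods; p from 0.1 to 0.6; tables built from the single records.

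- Record dated at first onset: period 1 shows p and period 2 shows p(1 − p), a relative loss of p in period 2.
- Record dated at the worst episode, equally likely to fall in either period: each period shows p(1 − p) + p²/2 = p − p²/2, a relative loss of p/2 in both.
- Ever-incidence over both periods is 1 − (1 − p)² and the mean episode count is 2p. The rule preserves both.

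| True p in each period | First-onset dating: period 1, period 2 | Worst-episode dating: each period | Ever | Mean count |
|---|---|---|---|---|
| 0.10 | 0.10, 0.09 | 0.095 | 0.19 | 0.2 |
| 0.20 | 0.20, 0.16 | 0.18 | 0.36 | 0.4 |
| 0.40 | 0.40, 0.24 | 0.32 | 0.64 | 0.8 |
| 0.60 | 0.60, 0.24 | 0.42 | 0.84 | 1.2 |

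Effect on the arm contrast in period 2 under first-onset dating:

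- True 0.60 against 0.20 is recorded as 0.60 × 0.40 = 0.24 against 0.20 × 0.80 = 0.16. The ratio falls from 3.0 to 1.5.
- True 0.60 against 0.40 is recorded as 0.24 against 0.40 × 0.60 = 0.24. A true difference of 0.20 disappears.

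Independence is probably generous to the rule. In general the share lost from period 2 is the probability that a patient with the event in period 2 also had it in period 1. If the same patients tend to have the event again, that share exceeds p.

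**The case against.** The case against has several parts, and much of it stands.

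- **Recurrences are counted.** Correct. A reader of the first sentence alone might infer that later episodes leave no trace, but the next sentence requires their number. The loss is of placement and grade, not of the count.
- **A decline over time is not built in.** Correct. A reader might infer that later rates must fall. That follows only if the record is dated at first onset. Under worst-episode dating there is no fall, though both periods are then too low. The protocol fixes neither convention.
- **Some repeat-course toxicity stays visible.** Correct. Serious events go on a separate form with onset date, duration and severity (8.7.5). Blood count, renal and liver tests are scheduled at day 29 and, for extended treatment, day 58 (section 5), and are summarised at each time point (10.7). Vomiting that affects compliance is documented (10.5), although the protocol does not make that an adverse event record with a grade.
- **Late follow-up is a different matter.** Correct. Beyond one month after treatment, non-serious events are missing because of the 8.7.4 window, not because of this rule.
- **The CRF is not at hand and might hold dates beside the count.** Possible, but the protocol does not ask for them, and it describes the record as a single entry at maximum level.
- **Section 10.7 promises no second-course table and the tables are descriptive.** Correct, and this limits the weight. It does not remove the mismatch with the stated description on treatment and during follow-up.

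A reader might also pair the 41 vomiting cases in the miltefosine row of Table 3 with the 63 in its cure column and derive a specific false difference between arms. The documents do not support this. Table 3 gives no denominator for side-effects, the row concerns miltefosine alone, and the protocol has no event rates by arm and period for this trial.

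**Conclusion.** The point holds for recurrent non-serious clinical adverse events between the first dose and one month after treatment. For these, one record at maximum grade with an undated count cannot support the planned description by period. It also cannot separate first course, extended course and the month after, and it may credit the grade and causality to the wrong period.

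The size cannot be derived from the protocol. Under the stated assumptions, first-onset dating understates later incidence by 10% at p = 0.1 and 60% at p = 0.6, more in the arm with more early events. Worst-episode dating understates both periods by half those fractions. The documents do not establish which of these would occur, so they do not demonstrate a bias between arms in a known direction.

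Whole-study ever-incidence, maximum grade per patient over the study, serious events, scheduled laboratory summaries and the day-29 primary analysis with its stopping boundaries are untouched. This is a cheap improvement of minor to moderate weight, limited to descriptive safety tables.

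**What to change.** Replace the single-record rule in section 8.7.5 with one CRF line per distinct episode, carrying onset date, stop date, grade and causality. In section 10.7, state that each episode is assigned to a period by its onset date. Tabulate patients with at least one episode in each period (initial course, extended course, one month after treatment), using the maximum grade within that period. The whole-study table of patients ever affected, at maximum grade, can stay beside it.

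The cost is revised CRF wording, more lines per patient and the double data entry that goes with them. No visit, sample or question is added, because section 8.7.3 already obtains these items at each questioning.
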